### Data management

Participating centres will be requested to record the data on paper data collection forms, enter them and send them electronically on a weekly basis to Geneva, using a Web-based system [14]. Recruitment and data quality will be monitored by the Programme's Statistics and Informatics Services Team using this system.

Data will be analyzed centrally in Geneva. Descriptive statistics will be calculated for all baseline characteristics for all subjects randomized, by treatment group, to describe characteristics of the population and to assess comparability of the groups. The overall summary statistics for women who complete the trial will be compared with those for the subjects lost to follow-up.

All subjects randomized having known outcome will be included in the main efficacy analysis in their randomized groups. If attempts fail to locate and contact a woman lost to follow-up, and her outcome of treatment is not known, then that woman will be excluded from the efficacy analysis. If she has information on side effects, she will be included in the safety analysis. Baseline characteristics of women lost to follow-up will be compared with those completing the study and between groups, to explore the possibility of bias due to these differences.

Crude rates for each outcome will be calculated in each arm and exact confidence intervals based on the binomial distribution calculated as described in Armitage and Berry [15]. If the interaction of misoprostol route by misoprostol dose is significant at 5% level, comparisons will be made between routes for each dose and between doses for each route. If the interaction is not significant at 5%, two comparisons will be made, between routes for the two doses combined, and between doses for the two routes combined. For these comparisons, relative risks (RR) of failure to achieve a complete abortion and failure to terminate pregnancy and the two-sided 95% CIs will be calculated by standard methods, as well as risk differences and two-sided 95% CIs. The latter will be used to test the non-inferiority hypotheses (at 2.5% level of significance) for achieving complete abortion.

Stratified analysis for efficacy will be conducted by gestational age (up to and including 49 days, 50–56 days and 57–63 days). Adjusted analysis by centre and for any prognostic variable showing imbalance at baseline will be performed using Mantel-Haenszel approach and/or logistic regression where appropriate. A per-protocol analysis will be performed excluding women with conditions as described in earlier sections. Efficacy will also be calculated excluding subjects with undetermined outcome. Survival analysis if appropriate will be used to compare the differences in induction-abortion intervals. Chi-square test or Fisher exact test as appropriate, will be used to compare the proportion of women with each side-effect, adjusting for multiple inferences with an appropriate technique.

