The results of our recent study [13] demonstrate an equivalent efficacy for both 24 h and 48 h intervals when 800 μg misoprostol is administered vaginally after mifepristone. As 24 h interval is more practical it is likely to become the standard in mifepristone-misoprostol regimens. This is why we chose the 24 h interval for the present trial.

The ultimate goal of our research is to improve the methods for termination of early pregnancy. The main objective of the present randomized trial is to compare four misoprostol regimens when administered either sublingually or vaginally 24 hours after 200 mg of mifepristone, among women with a gestational age of up to 63 days. The four regimens will be compared in respect of the following main outcomes: (i) their efficacy to induce complete abortion; (ii) induction-to-abortion interval, when possible; (iii) the occurrence of side-effects; and (iv) women's perceptions.

Although there are no comparative studies the efficacy might be somewhat lower if the dose of misoprostol is reduced. If, however, the side-effects will decrease and the regimen is more acceptable to women, it would be justified to use a lower dose if non-inferiority is demonstrated within a margin of 3%. Our hypothesis is that the efficacy of 400 μg misoprostol, whether given sublingually or vaginally after mifepristone pretreatment, is not inferior to that of 800 μg misoprostol within a margin of 3%.

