#### Number of subjects and statistical power

To establish the non-inferiority (one-sided equivalence) of the 400 μg misoprostol (sublingual or vaginal) regimen compared to the 800 μg with respect to efficacy, we require the upper limit of the one-sided 95% confidence interval (or the two-sided 95% confidence interval) for a difference in complete abortion rates (that of 800 μg minus that of 400 μg) to be within a margin of equivalence of 3%. It is estimated that if the abortion rates in the two regimens are both equal to 95%, about 680 subjects will be required in each group to demonstrate non-inferiority with a power of 80%, i.e. a total of about 2720 subjects. To allow for a 5% of women lost to follow-up or with undetermined outcomes, then about 720 women will have to be recruited per group, a total of about 2880. If 15 centres participate in the study, 192 subjects will be needed in each centre. However, to ensure recruitment in one year time, we plan to include one additional centre, 16 centres in all. Since we plan to take four packs per centre for quality control, the actual number of women recruited per centre will be 188. These calculations allow for the presence of an interaction between misoprostol dose and its route of administration.

For the choice of the non-inferiority margin, a clinical criterion was used, not a statistical one. This is based on the fact that there are not placebo-controlled trials available and the efficacy of placebo would be close to zero. We set the margin at 3% based on clinical assessment that this difference is not relevant.

It is estimated that the trial will require 12 to 14 months for data collection at each centre and between 6 and 12 months of centralized data analysis in Geneva.

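### The per-route test of 400 against 800 μg is run only if a weak interaction test is significant, so a routes-combined pass could be read as a claim for each route that was never tested

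*Protocol article*

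**What the plan says.** All references are to the protocol article.

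- **Data management, interaction significant at 5%:** "comparisons will be made between routes for each dose and between doses for each route".
- **Data management, interaction not significant:** "If the interaction is not significant at 5%, two comparisons will be made, between routes for the two doses combined". The second of the two is one 800-versus-400 comparison that merges the routes. No within-route dose comparison is listed in this branch.
- **Data management, test:** the risk differences and their two-sided 95% CIs carry the decision: "The latter will be used to test the non-inferiority hypotheses (at 2.5% level of significance) for achieving complete abortion".
- **Background, hypothesis:** the efficacy of 400 μg, "whether given sublingually or vaginally after mifepristone pretreatment, is not inferior to that of" 800 μg, within 3%. The same section also gives a separate expectation that the lower vaginal dose will suffice.
- **Number of subjects and statistical power:** about 680 evaluable women in each of four groups, with the comment "These calculations allow for the presence of an interaction between misoprostol dose and its route of administration". The criterion is the "upper limit of the one-sided 95% confidence interval (or the two-sided 95% confidence interval) for a difference in complete abortion rates".

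**The concern.** The hypothesis and the sample size are set out by route, but the default analysis is not. A non-significant interaction test removes the two within-route comparisons and leaves one dose difference averaged over routes. Absence of a significant interaction is weak evidence that the routes behave alike when the test has little power. In a non-inferiority trial the averaging also works in the direction of success: a route with no dose difference pulls the combined difference towards zero and away from the margin.

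At stake is the wording of the main conclusion. If the pooled upper limit is below 3% and the result is reported in the terms of the Background hypothesis, the trial will have concluded non-inferiority for a route whose own difference was never tested against the margin.

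**Working it through.** **Inputs from the article.** Margin 3 points; planning rate 95% in both doses; about 680 evaluable per group for 80% power; 5% loss; 3008 women in four groups; interaction tested at 5%; non-inferiority tested at 2.5% one-sided.

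**Assumptions.** The 400 μg rates below are mine, since the article gives none other than the planning rate. The interaction scale is not stated, which an article may leave out, so both the risk-difference (RD) and log-odds scales were run. Interim looks, centres and gestational strata are ignored.

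**1. The plan's own sample size.** The simple formula is n = 2p(1−p)(z_α + z_β)² / margin², with 2 × 0.95 × 0.05 / 0.03² = 105.56.
- One-sided 5%: 105.56 × (1.645 + 0.842)² gives 653. The Farrington-Manning version gives 683, which matches the stated 680.
- One-sided 2.5%: 105.56 × (1.960 + 0.842)² gives 829. Farrington-Manning gives 869.

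So 680 reproduces at one-sided 5%, not at the 2.5% of the Data management section. For 5% loss, 680/0.95 = 716, against the stated 720. The planned total gives 3008/4 = 752 per arm, and 752 × 0.95 ≈ 714 evaluable.

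**2. Power of the interaction test, by hand.** Take one route at 95% vs 92% and the other at 95% vs 95%, with 714 per arm. The SE of the difference between the two route-specific differences is √[(3 × 0.0475 + 0.0736)/714] = 0.0174. Then 0.03/0.0174 = 1.72, and Φ(1.72 − 1.96) ≈ 0.41. On the log-odds scale the simulated power is 33%.

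**3. The two-stage rule, simulated.** Each scenario used 400,000 trials, 714 per arm and Wald intervals. The fourth column is the share of trials in which the interaction is not significant and the pooled upper limit is below 3%. The last column is the pass rate of the worse route's own test.

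| Worse route, 800 vs 400; other route | True average difference | Interaction power, RD / log-odds | Pooled pass via the gate | Worse route's own test |
|---|---|---|---|---|
| 95 vs 92; 95 vs 95 | 1.5 | 41% / 33% | 26.0% / 27.4% | 2.6% |
| 95 vs 92; 95 vs 96 | 1.0 | 65% / 58% | 24.8–27.0% | 2.6% |
| 95 vs 92; 95 vs 94 | 2.0 | 20% / 16% | 16.9–17.2% | 2.6% |
| 95 vs 91; 95 vs 95 | 2.0 | 62% / 49% | 9.5–10.5% | 0.4% |
| 95 vs 90; 95 vs 95 | 2.5 | 79% / 64% | 2.5–2.9% | 0.04% |
| 95 vs 92; 95 vs 92 | 3.0 | 5% / 5% | 2.5% | 2.7% |

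The last row shows that the pooled test is correctly sized for the averaged difference.

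**4. Sensitivity of the first row.**
- With 680 per arm the pooled-pass figure is 25.7–26.9%; with 752 it is 26.2–27.9%.
- With the one-sided 95% interval that the sample-size section also allows, it is 33–36%.
- With the 800 μg rates that the Background cites from a study of 224 women (93.8% vaginal, 98.2% sublingual) and the vaginal low dose 3 points worse, it is about 35% (RD) or 40% (log-odds).

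**5. Power of the alternative, all arms at 95%.**
- One route at one-sided 2.5%: 0.03/√(0.095/714) = 2.60, and Φ(2.60 − 1.96) ≈ 0.74.
- Both routes: 0.74² ≈ 0.55.
- Gated rule: pooled power is about 0.96. Multiplied by the 0.95 chance of a non-significant interaction, this gives about 0.91.

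**The case against.** The strongest reply is that the pooled pass is a correct answer to the question the rule asks. In the first five scenarios the true routes-combined difference lies inside the margin (1.0 to 2.5 points), and when both routes are at the margin the test passes 2.5% of the time. A reader might infer that the plan's 2.5% error rate fails. The documents do not support that: the analysis text labels the comparison as routes combined, and nowhere says that a pooled pass will be reported as a claim for each route. The Background hypothesis can also be read as a dose effect across routes. This stands, and it limits the point: 26–27% is an error rate only under the route-specific reading.

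The article also has partial safeguards. Crude rates with exact intervals are given for every arm whatever the interaction result, so a poor route would be visible. Dropping a lower-dose regimen for low efficacy rests on comparison with vaginal 800 μg. Neither is a within-route dose difference set against the 3% margin.

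The statement that the calculations allow for an interaction does not answer the concern. It describes the size of each group for the dose comparison, not power to detect an interaction, and the per-group comparison is then not made in the default branch.

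Finally, the headline scenario lies near the peak of the effect. A reader might infer inflation of that size wherever a route is beyond the margin. It falls to about 10% at 1 point beyond and to 2.5–2.9% at 2 points beyond.

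**Conclusion.** The concern holds in a limited form and should be fixed. The gate is an inadequate basis for choosing between a per-route and an averaged conclusion, because the interaction test has about 33–41% power in the pattern that matters most. If a pooled pass is read as applying to each route, as the Background wording invites, it would be wrong in about 26–27% of trials with one route at the margin and the other at no difference. The figure is about 17% if the other route is 1 point worse, and about 9–10% if the worse route is 1 point beyond the margin. That route's own test would pass in about 2.6% of trials or fewer.

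These figures assume 714 evaluable women per arm, a 95% rate on 800 μg and 400 μg rates that I chose. The conclusion does not depend on the scale of the interaction test. It does depend on how a pooled pass is worded in the report, which the article leaves open.

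**What to change.** 1. Whatever the interaction result, report the 800-minus-400 risk difference with its two-sided 95% CI within each route.
2. Allow a non-inferiority claim for a route only if that route's own upper limit is below 3%.
3. Label the routes-combined result as the average dose effect.
4. Report the interaction as an estimate with a CI, not as a gate.
5. Restate the power of the per-route comparison at the significance level actually used.

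Items 1 to 4 are changes of wording and need no new data. The cost is power. With all arms at 95% and a one-sided 2.5% test, power is about 74% for each route and 55% for both, against about 91% for declaring both under the gated rule. At 680 per group it is about 72% per route: Φ(0.03/√(0.095/680) − 1.96) = Φ(0.58). Reaching 80% per route at that level would take 829 to 869 evaluable women per group. If the sample stays as planned, the plan should say openly that the per-route claims are underpowered and that the average dose effect is the better-powered result.

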It has recently been demonstrated that sublingual administration of misoprostol might be an alternative to vaginal treatment. Pharmacokinetic studies have shown that the plasma levels of misoprostol were higher and the area under the curve of misoprostol concentration versus time up to 360 minutes was significantly greater than those following oral and vaginal administration [5]. After sublingual administration the increase in uterine tonus is more rapid and more pronounced than after vaginal administration, but the contractions start to decrease after about 3 hours compared to 4–5 hours after vaginal dose [7,8]. In a pilot study using misoprostol alone [9], a dose of 600 μg was administered sublingually every 3 hours for a maximum of 5 doses to women requesting medical abortion at up to 12 weeks gestation. The overall complete abortion rate was 86%. Diarrhoea, fever and chills were the most common side-effects. Almost all women who had a complete abortion would have chosen this method again. The sublingual route was regarded as convenient and gave more privacy during the abortion process.

In a recent study undertaken in collaboration with our Programme [10], 800 μg misoprostol was administered either vaginally or sublingually after pretreatment with mifepristone for termination of pregnancy. The study included 224 women up to 63 days of gestation. Complete abortion rates were 93.8% and 98.2% after vaginal and sublingual administration, respectively, indicating that the sublingual route could be superior to the vaginal. However, the incidence of side-effects was higher after sublingual administration. Another study also suggested a very high efficacy after sublingual administration of 600 μg of misoprotol among 96 women treated, as 93 of them (98.9%) had a complete abortion [11].

No previous studies have tested 400 μg dose of misoprostol, either sublingual or vaginal, in the first trimester. It does not seems logical to administer a dose for vaginal use that is twice as high as the dose recommended for oral use when scientific data shows the vaginal route to be more efficient. It seems also relevant to test the possibility that sublingual administration might be at least as effective as vaginal administration since a non-vaginal route of administration is preferred by many women [9,12].

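### The two-stage dose rule does not hold its stated 2.5% level (about 4.2% if either within-route pass counts), and route is drawn into the non-inferiority tests without a margin

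*Protocol article*

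**What the plan says.** The Data management section of the protocol article sets a gate: "If the interaction of misoprostol route by misoprostol dose is significant at 5% level", then "comparisons will be made between routes for each dose and between doses for each route". Otherwise "two comparisons will be made, between routes for the two doses combined, and between doses for the two routes combined". Relative risks and risk differences with two-sided 95% intervals are computed for whichever set applies, and of the risk-difference intervals it says: "The latter will be used to test the non-inferiority hypotheses (at 2.5% level of significance) for achieving complete abortion". The Methods part of the Abstract describes the same scheme for routes and doses together.

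The hypothesis itself is stated for dose only. Background says that the efficacy of 400 μg, "whether given sublingually or vaginally after mifepristone pretreatment, is not inferior to that of 800 μg misoprostol within a margin of 3" per cent. Number of subjects and statistical power gives the sign (800 μg minus 400 μg) and requires the upper limit "to be within a margin of equivalence of 3" per cent. For route, Background says only that it is relevant to test whether "sublingual administration might be at least as effective as vaginal administration".

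Adjustment for multiple inferences is mentioned only for side-effects. The Haybittle-Peto rule deals with the interim looks, not with the number of contrasts.

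**The concern.** The level of 2.5% is attached to each test, but the dose conclusion comes from a two-stage procedure. The same data decide whether dose is tested once (pooled) or twice (within each route). A significant interaction means that the two within-route differences lie far apart, so one of them is likely to look favourable by chance. If that one pass is read as showing 400 μg to be non-inferior, the procedure exceeds 2.5%. Nothing in the section says whether one pass or both are needed, so the error rate of the trial's central claim is not fixed.

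There is also a gap for route. The sentence on non-inferiority tests grammatically includes the route comparisons, yet no route margin or formal route hypothesis appears. A route non-inferiority test cannot be carried out as written.

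**Working it through.** **Inputs.** The one-sided level of 2.5%, interaction gate of 5% and two-stage rule come from Data management. The 3-point margin, 95% complete abortion rate and 5% loss come from Number of subjects and statistical power. Arm size: 3008 / 4 = 752 randomized, and 752 × 0.95 = 714 evaluable.

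**Assumptions.** The dose null sits at its boundary in both routes (95% for 800 μg, 92% for 400 μg), with no route effect and no true interaction. Intervals are Wald, and the interaction is a z test on the risk-difference scale. No route margin is needed.

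**1. The plan's own figure.** The pooled dose test alone gives 2.5% in normal theory and 2.6% in binomial simulation. The stated level therefore holds for that test.

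**2. Why the switch matters.**
- Within-route standard error: √[(0.95×0.05 + 0.92×0.08)/714] = √(0.1211/714) = 0.0130.
- A within-route test passes if the observed loss is below 3 − 1.96 × 1.30 = 0.45 points.
- The interaction is significant if the two within-route losses differ by more than 1.96 × √2 × 1.30 = 3.6 points. In such trials the smaller loss has been pulled well down.
- In simulation, at least one within-route dose test passes falsely in 34.9% of trials with a significant interaction (33.8% in normal theory).
- Both almost never pass together. With the larger loss at 0.45 points, the smaller would have to be about 0.45 − 3.6 = −3.15. That is 6.15 points from the truth, or about 4.7 standard errors.

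**3. The rule as a whole.** The interaction test rejects in about 5% of these trials.
- Either pass counts: 0.95 × 2.61% + 0.05 × 34.9% = 2.48% + 1.75% = 4.2%. Direct simulation also gives 4.2%; normal theory gives 0.95 × 2.5% + 0.05 × 33.8% = 4.1%.
- A given route (pooled pass, or that route's own pass): 2.48% + 0.05 × (34.9% / 2) = 2.48% + 0.87% = 3.4%.
- Both passes required: 2.48% + about 0 = 2.5%.

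**4. Power cost of requiring both, 95% in all arms.** Pooled, 2 × 714 = 1428 per dose: standard error √(2×0.0475/1428) = 0.00816; 0.03/0.00816 − 1.96 = 1.72; power about 96% (95.6% simulated). Requiring both within-route passes keeps 0.95 × 95.6% = 90.8%, plus a small contribution from trials with a significant interaction, so about 91%.

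**5. If route is also tested.** This needs an assumed 3% route margin with vaginal as reference, and both factors exactly at the margin (for example 95/92/92/89%). Either pooled test then gives 1 − 0.975² = 4.9% (5.1% simulated), and the full two-stage rule gives about 7.4% to 7.6%.

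**The case against.** The strongest reply is that the dose hypothesis in Background covers 400 μg by either route, which supports requiring both within-route passes. Scored that way, the rule as written already runs at about 2.5%. This is a fair reading and the one adopted in the fix. It is not stated in Data management, however, where each within-route comparison simply has its own 2.5% test. The excess depends on a choice that the plan leaves open.

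Second, hierarchy and rules for mixed results are often left to an analysis plan, and only a condensed article is at hand. That is right for fine detail, and it is why the absence of an alpha split is not pressed here. But the article does fix a level and a two-stage rule, and the two do not agree unless the missing scoring rule is supplied.

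Third, a reader might infer that the trial has no primary contrast and a false-claim rate of 5% to 7.5%. The documents do not support this. Dose is the only hypothesis stated, with margin and sign, and it is the sole basis of the sample size. The higher range needs a route margin that the protocol never gives, and sublingual exactly 3 points worse than vaginal. The one direct route comparison cited in Background points the other way (98.2% sublingual, 93.8% vaginal). Testing each factor of a factorial trial at its own full level is also a common and defensible convention.

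Fourth, the reference route is not wholly open: Background implies vaginal as comparator. Only the margin and the formal hypothesis are missing.

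**Conclusion.** The point holds in a limited form. For the dose hypothesis, the two-stage rule does not guarantee 2.5%. At the boundary in both routes, with 714 evaluable women per arm, the false-claim rate is about 4.2% if either within-route pass counts (4.2/2.5 = 1.7 times the stated level) and about 3.4% for a given route. It is about 2.5% if both are required. These figures rest on Wald intervals, no true interaction and equal routes, but on no assumption about a route margin.

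For route, the finding is one of wording: Data management and the Abstract include it in the non-inferiority tests, while margin and sign exist only for dose. The 5% to 7.5% any-claim rate is a conditional worst case and should not be quoted as the trial's error rate.

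**What to change.** In Data management:

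1. State that the dose contrast for complete abortion (800 μg minus 400 μg, 3% margin, one-sided 2.5%) is the confirmatory test.
2. After a significant interaction, claim non-inferiority of 400 μg for both routes only if both within-route upper limits are within 3%. Report a single-route pass as a route-specific result, without the 2.5% guarantee.
3. For route, either report the estimate with its confidence interval and make no non-inferiority claim, or state the reference (vaginal, as Background implies) and a margin before data are seen.

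Making the route test conditional on success for dose is optional. It would make a sound route result descriptive whenever dose non-inferiority is not shown.

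The cost is a few sentences and no extra patients. The pooled test is unchanged. The power of the overall dose claim, at 95% in all arms, falls from about 96% to about 91%, because some 5% of trials would show a chance interaction and then seldom meet both limits.
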